## Procedures

### Body Mass

Body mass weight will be measured (Tanita BWB-627A, Tokyo, Japan) and recorded to the nearest  $\pm 0.1$  kg upon arrival at all study visits. The recorded body mass during visit 1 and visit 2 will be compared to ensure the participant is weight stable and any participant whose body mass changes by more than 3% during this time will be excluded from participation. In addition, body weight will be assessed to compare changes seen after completion of the supplementation and resistance training protocols.

### Body Composition Assessment

To achieve the highest levels of sensitivity and accuracy, a four-compartment body composition model will be employed according to the methods of Wilson et al. 2013 (Wilson, Fan et al. 2013) and Smith-Ryan et al. 2017 (Smith-Ryan, Mock et al. 2017). Body volume and bone mass will be assessed using a dual-energy x-ray absorptiometry (DEXA) scan (Hologic QDR Discovery A, Waltham, MA) on four separate occasions (visits 2, 3, 4, and 5). In addition, the lean tissue component will be estimated to quantify lean and fat-free body masses for each participant. Participants will be required to observe an overnight fast in order to ensure an accurate determination of body composition and hydration will be standardized using urine specific gravity measurements by a urine refractometer. All DEXA scans will occur during the hours of 0600 and 1000 by graduate assistants or faculty trained in DEXA administration and analysis. Prior to each

day of testing, the device will be calibrated according to manufacturer guidelines. All scans will be completed according to device specifications.

### ***Urine Specific Gravity***

Using a handheld refractometer and prior to each DEXA, participants will donate a mid-stream urine sample for determination of their urine specific gravity and assessment of hydration status. Using a transfer pipet, approximately 500uL of urine will be transferred onto the refractometer and compared against a standardized evaluation scale. Urine specific gravity values above 1.020 will be deemed as a dehydrated sample. Participants will be required to remain in the lab consuming water until they produce a urine specific gravity sample that is below 1.020. To encourage optimal hydration upon arrival, participants will be given instructions to follow to ensure proper hydration levels are achieved.

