### Baseline Testing (Visit 2)

At least three days after Visit 1 to allow for completion of their food record, participants will return to the lab to complete their first testing session and begin following the resistance training and supplementation regimens. Participants will first have their body mass assessed before providing a urine sample and completing their body water, DEXA assessments (i.e. 4-compartment assessment), and muscle thickness via ultrasound. This scan will be done between the hours of 0600-1000 following an overnight fast and hydration levels will be standardized through the use of urine specific gravity measurements using a hand-held refractometer. Participants will be sent a hydration protocol to follow 24 hours prior to their visit to help ensure adequate hydration levels. This protocol will instruct the participants how much water they should be consuming throughout the day. Prior to testing, participants will complete the same standardized warm-up consisting of 5 minutes of light cycling, 10 body weight squats, 10 body weight walking lunges, 10 dynamic walking hamstring stretches (straight-leg march), and 10 dynamic walking quadriceps stretches. After the warm-up,

participants will complete five CMJ with their hands on their hips. One minute of rest will be observed between each CMJ. Participants will have their maximal voluntary isometric contraction (MVC) completed using an isometric mid-thigh pull. Three attempts will be made and one minute of rest will be observed between each test. Participants will then have their 1RM determined using the leg press exercise. Three minutes of rest will be provided after 1RM is determined and each participant will perform repetitions to failure using 80% of their previously determined 1RM to determine their repetitions to fatigue (RTF). An additional 3-minute break will be observed and then bench press 1RM and RTF will be completed using identical procedures as the leg press exercise. After observing a three-minute rest period after completion of the bench press RTF participants will complete a Wingate using a load that is equivalent to 7.5% of their body mass to measure anaerobic capacity (Lode Excalibur Sport, Lode, Netherlands). Participants will then complete an education session with a research team member to outline the dietary goals they are required to meet throughout this study. This study visit will take approximately 90 minutes to complete.

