#### Resistance Training & Supplementation Phase (Visits 3 and 4)

After completing two weeks of resistance training (8 total workouts), participants will return to the lab at a similar time (0600 – 1000 hours) for completion of an identical bout of testing. Prior to this visit, participants will complete another three-day food record and discuss with research team members about their compliance to the diet program. Participants will also have their body mass recorded. Participants will then donate a urine sample to assess hydration before completing a body water, DEXA, and ultrasound assessment. Using identical procedures as before, participants will have their CMJ performance, maximal strength (1RM and isometric mid-thigh pull) and endurance (maximal repetitions at 80% 1RM [RTF]) assessed before completing a Wingate anaerobic capacity test (WanT). New 1RM values will be used to re-assign loads during the following resistance training period. This visit will take approximately 90 minutes to complete.

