#### Final Study Visit (Visit 5)

Approximately ten weeks after beginning the resistance training (40 workouts; a minimum of 36 required or 90% compliance) and supplementation protocol, study participants will report back to the lab for their final study visit during a similar time of day (0600 – 1000 hours). In an identical fashion as previously completed, participants will observe an overnight fast, ensure completion of all food and training records, return any remaining supplements and have their body mass, hydration, body water, body composition (DEXA), ultrasound, countermovement jump, maximal strength (bench

press 1RM, leg press 1RM, and isometric mid-thigh pull), muscular endurance (repetitions to failure using 80% [RTF] of their Visit 2 1RM for both exercises) and anaerobic capacity (WanT) determined. This visit is estimated to take 90 minutes to complete.

**Table 1:** Outline of testing for the 10-week study.

| Procedure                                     | Pre-Study
(Visit 1) | Week 0
(Visit 2)                                                                | Week 2
(Visit 3) | Week 6
(Visit 4) | Week 10
(Visit 5) |
|-----------------------------------------------|------------------------|------------------------------------------------------------------------------------|---------------------|---------------------|----------------------|
| Resistance Training Protocol                  |                        | [figure not shown] |                     |                     |                      |
| Supplementation Protocol                      |                        | [figure not shown] |                     |                     |                      |
| Review & Sign Consent                         | X                      |                                                                                    |                     |                     |                      |
| Screening (Health, Medical, Exercise History) | X                      |                                                                                    |                     |                     |                      |
| Height and Weight                             | X                      | X                                                                                  | X                   | X                   | X                    |

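### Body mass is taken on arrival, before any water drunk to clear the urine check; with no second weighing stated, the four-compartment inputs can describe different body states

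*Protocol*

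**What the plan says.** The Body Mass section has weight recorded "upon arrival at all study visits". The visit descriptions give the same order:

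- Visit 2: "Participants will first have their body mass assessed before providing a urine sample and completing their body water, DEXA assessments".
- Visits 3 and 4: body mass is recorded, then "Participants will then donate a urine sample to assess hydration before completing a body water, DEXA, and ultrasound assessment".
- Visit 5: "In an identical fashion as previously completed", with body mass listed ahead of hydration, body water and DEXA.

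Under Urine Specific Gravity, a reading above 1.020 counts as dehydrated, and "Participants will be required to remain in the lab consuming water until they produce a urine specific gravity sample that is below 1.020". Neither the volume drunk nor the time is limited, and no section mentions a second weighing.

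Under Body Composition Assessment, "a four-compartment body composition model will be employed". DEXA supplies body volume and bone mass, and impedance supplies body water (Body Water Assessment).

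The protocol is not consistent about which fat-free mass is analysed. Question 14 and Experimental Design say that fat-free, lean and fat mass come from the four-compartment model. Statistical Analysis names the Week 10 minus Week 2 change in DEXA fat-free mass as a primary endpoint. The Dependent Variables list gives fat-free mass as primary without naming a method.

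**The concern.** A four-compartment equation combines mass, volume, water and bone on the premise that all four describe the same body at the same moment. For a participant who fails the first urine check, the stated order puts the weighing before the water and the volume and water measurements after it. The equation gets fat from a difference between volume and mass terms, so the mismatch is enlarged rather than passed through one for one.

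The error arises only at visits where the first sample fails. If that happens at Week 10 but not at Week 2, or the reverse, it goes in full into the change score. The result is avoidable measurement noise in outcomes compared with 12 participants per arm.

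**Working it through.** The protocol gives no figure on this point, so there is nothing to reproduce. The check has two parts.

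**Order of measurements.** Body Mass and the descriptions of Visits 2 to 5 agree: weigh, test urine, then body water and DEXA. The drinking rule falls between the urine test and the scans. The arrival weight is the only scale weight described.

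**Size, as an illustration.** Let M be mass, V volume, F fat, W water, B bone mineral and R residual.

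M = F + W + B + R, and V = F/dF + W/dW + B/dB + R/dR.

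Eliminating R and solving for F:

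F = [V − M/dR − W(1/dW − 1/dR) − B(1/dB − 1/dR)] / (1/dF − 1/dR), and fat-free mass = M − F.

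Assumptions, none of them from the protocol:

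- Densities in kg/L: dF = 0.90, dW = 0.994, dR = 1.34 to 1.52. Bone is unchanged, so its density drops out.
- Net water retained after weighing (drunk minus passed): w = 0.25 to 0.5 kg.
- The scan registers the full added volume, w/dW.

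Hold M at its arrival value.

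*Impedance registers the water* (W rises by w): change in F = w(1/dR)/(1/dF − 1/dR) = w × dF/(dR − dF).

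- dR = 1.34: 0.90/0.44 = 2.05 kg per kg of water.
- dR = 1.52: 0.90/0.62 = 1.45 kg per kg.

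*Impedance does not register it* (W unchanged): change in F = w(1/dW)/(1/dF − 1/dR).

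- dR = 1.34: 1.0060/(1.1111 − 0.7463) = 2.76 kg per kg.
- dR = 1.52: 1.0060/(1.1111 − 0.6579) = 2.22 kg per kg.

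| Net water (kg) | dR | Fat overstated, registered (kg) | Fat overstated, not registered (kg) |
|---|---|---|---|
| 0.25 | 1.34 | 0.51 | 0.69 |
| 0.25 | 1.52 | 0.36 | 0.55 |
| 0.5 | 1.34 | 1.02 | 1.38 |
| 0.5 | 1.52 | 0.73 | 1.11 |

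Because M is fixed, fat-free mass is understated by the same amounts relative to the arrival state.

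**With mass re-taken at the scan** (M also rises by w):

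- If impedance registers the water, the change in F is 0 and fat-free mass rises only by the water itself.
- If it does not, the change in F = w(1/dW − 1/dR)/(1/dF − 1/dR). For 0.5 kg this is 0.5 × 0.2598/0.3648 = 0.36 kg (dR = 1.34) or 0.5 × 0.3481/0.4532 = 0.38 kg (dR = 1.52), against 1.38 and 1.11 kg without re-weighing.

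**The case against.** Four objections carry weight.

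1. **Primary endpoint.** A reader might infer that the primary endpoint is compromised. The documents do not establish that. Statistical Analysis names DEXA fat-free mass, and Supplementation Protocol matches participants on it. A value read directly from DEXA does not use the scale weight, so it carries no mass mismatch and re-weighing would not change it. Question 14 and Experimental Design point the other way. The effect on the primary endpoint therefore depends on a conflict the protocol leaves open.

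2. **Which mass enters the model.** Body Mass gives two uses for the arrival weight: the weight-stability check and the description of weight change. Neither is the four-compartment equation, and the model is specified by reference to published methods. That the arrival weight is the input is an inference, though no other scale weight is described. The data collection form and the hydration protocol are attached but not shown. They cannot be assumed to include a second weighing, nor to exclude one.

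3. **Size.** The volume retained and the densities are assumed. Urine is passed after the weighing, both for the first sample and for the repeat, so net retention is less than the amount drunk. The figure near 1.0 kg is the top of the range when impedance registers the water.

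4. **Power and bias.** A reader might infer a definite loss of power, or a tilt towards one arm. Neither is supported. The protocol gives no share of visits at which the first sample fails, and its advance hydration instructions should lower that share. Allocation is randomised and double-blind, so failures should not favour an arm.

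What survives is the order itself. It is explicit, and no section corrects it.

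**Conclusion.** The point holds as a modest flaw in measurement procedure. Followed as written, the protocol lets the only described mass predate the volume and water inputs whenever a participant has to drink to clear the urine check. The illustrative misstatement is roughly 0.4 to 1.0 kg if impedance registers the water and up to about 1.4 kg if it does not. It rests on the assumed densities, on 0.25 to 0.5 kg of net retained water, and on the arrival weight being the model's mass input. Drinking adds no such error at visits where the first sample clears.

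The consequence is extra noise in the four-compartment outcomes in all arms, of unknown frequency. No power figure can be attached to it. Whether a primary endpoint is touched depends on which fat-free mass the trial analyses.

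**What to change.** Add to Urine Specific Gravity, and align Body Mass with it, that body mass is taken again after the urine check has cleared and the participant has voided, immediately before impedance and DEXA, and that this value enters the four-compartment model. Keep the arrival weight for the weight-stability rule. The visit descriptions already call for identical procedures, so they need little change.

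Separately, reconcile Statistical Analysis with question 14 and Experimental Design on whether the primary fat-free mass is the DEXA value or the four-compartment value.

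The cost is one short repeat weighing on the same scale at a testing visit and one extra data field. If impedance does not register recently drunk water, re-weighing reduces the error but does not remove it.

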### ***Body Water Assessment***

Total, intracellular, and extracellular body waters will be assessed using an InBody 570 bioelectrical impedance analyzer on four separate occasions (visits 2, 3, 4, and 5). Participants will be required to observe an overnight fast to ensure an accurate determination of body composition. All BIA assessments will occur between 0600 – 1000 hours by trained research personnel. Prior to each day of testing, the device will be calibrated and all assessments completed according to manufacturer guidelines.

### ***Ultrasound Assessment***

The Ultrasound (GE Doppler Ultrasound Scanner) will be used on four separate occasions (visits 2, 3, 4, and 5) to complete muscle thickness measures with a 3 to 12 MHz multi-frequency linear phase array transducer (Logiq S7 R2 Expert; General Electric). The ultrasound wand will be placed on the participant's vastus lateralis (outer thigh muscle) midway between the iliac crest (hip crease) and patella (knee) of the dominant leg while the participant is lying in a supine (on their back) position on an exam table. During the assessment, the research team member will be able to determine the thickness of the participant's thigh.

### ***Maximal Strength - One-Repetition Maximum (1RM)***

Maximal strength will be determined through assessment of the one-repetition maximum (1RM) using the bench press (upper-body) and leg press (lower-body) exercises on four separate occasions (visits 2, 3, 4, and 5). For each assessment, a standardized warm-up consisting of simple stretches and whole-body movements will be completed before performing one set of ten repetitions at 50% of their perceived 1RM. After a rest period of two minutes, participants will perform one set of six repetitions with 70% of their perceived 1RM and then an additional set of four repetitions with 85% of perceived 1RM. From there, one-repetition sets will be completed with progressively increasing loads with two minutes of rest between sets until a 1RM is determined. The 1RM for each exercise will be determined within three to five 1RM attempts to prevent accumulative fatigue from confounding subsequent attempts. Trained investigators will be present during all testing to ensure proper technique is followed for all attempts. Participants will rest for three minutes between determination of their 1RM and completion of the next test.

### ***Muscular Endurance - Repetitions to Failure (RTF)***

Muscular endurance will be assessed using the bench press (upper-body) and leg press (lower-body) exercises on four separate occasions (visits 2, 3, 4, and 5). To complete this assessment, study participants will use a load that corresponds to 80% of their Visit 2 1RM for both the bench press and leg press exercises and will be instructed to complete as many repetitions as they can until failure for one set of each exercise. Failure will be defined as resting for more than two seconds throughout any point on the exercise set or technique failure. Total training volume (set x repetitions x load) will be computed and recorded. All subsequent repetitions to failure tests (weeks 2 and 10) will use a load that corresponds to 80% of their visit 2 1RM value.

### ***Wingate Anaerobic Capacity Test (WanT)***

Participants will complete a Wingate anaerobic capacity test on four separate occasions (visits 2, 3, 4, and 5) on a Lode Excalibur Sport computerized ergometer (Lode, Netherlands). The testing protocol will begin with five-minute warm-up consisting of light pedaling against zero resistance. The resistance for Wingate testing will be set at 7.5% of body weight (kg) for each participant. Participants will be able to see how much time is left in their warmup and instructed to increase their pedaling speed so they reach their maximal cadence when approximately five seconds remain in the warm-up. Participants will be verbally encouraged to continue pedaling as fast as they can throughout the entire 30-second protocol. Peak power, average power, and time to fatigue will be computed and used as indicators of anaerobic power and fatigue resistance.

### ***Resistance Training Program***

#### *Layout of Resistance Training Program*

A template of the resistance training program is outlined in Table 2. Participants will be required to complete a daily online checklist of their workout progress and schedule the completion of at least one workout per week under the direct supervision of a research team member inside the Fieldhouse. Intensity will increase throughout the study to ensure a progressive overload to facilitate increases in strength and muscle mass. For the first six weeks (weeks 1-6), each workout will consist of 3 sets of 10 repetitions to momentary muscular failure. The final four weeks (weeks 7-10), 4 sets of 6 repetitions will be completed. One minute of rest in between sets will be allotted for weeks 1-6 while two minutes of rest between each set will be followed for weeks 7-10.

Table 2: Overview of resistance training program

| Weeks | Monday, Thursday                                                                                                                                                                                   | Tuesday, Friday                                                                                                                                                                             |
|-------|----------------------------------------------------------------------------------------------------------------------------------------------------------------------------------------------------|---------------------------------------------------------------------------------------------------------------------------------------------------------------------------------------------|
| 1-6*  | Bench press, 3x10
Chest flies, 3x10
Lat pull, 3x10
Seated row, 3x10
Shoulder press, 3x10
Shoulder shrugs, 3x10
Bicep curls, 3x10
Triceps extensions, 3x10
Bench press, 4x6 | Back squat or leg press, 3x10
Leg extensions, 3x10
Deadlift, 3x10
Lunges, 3x10
Lying leg curls, 3x10
Calve raises, 3x10
Ab crunches, 3x25
Back squat or leg press, 4x6 |

|       |                         |                      |
|-------|-------------------------|----------------------|
| 7-10‡ | Chest flies, 4x6        | Leg extensions, 4x6  |
|       | Lat pull, 4x6           | Deadlift, 4x6        |
|       | Seated row, 4x6         | Lunges, 4x6          |
|       | Shoulder press, 4x6     | Lying leg curls, 4x6 |
|       | Shoulder shrugs, 4x6    | Calve raises, 4x6    |
|       | Bicep curls, 4x6        | Ab crunches, 3x25    |
|       | Triceps extensions, 4x6 |                      |

\*One minute rest between sets

‡Two minutes rest between sets

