**STATISTICAL ANALYSIS:**

All analyses will be completed using Microsoft Excel and the Statistical Package for the Social Sciences (v23; SPSS Inc., Chicago IL). Before any statistical tests are performed, data will be analyzed for normality, skewness, and kurtosis. All non-normal data will be log-transformed prior to analysis. For all statistical tests, data will be considered statistically significant when the probability of a type I error is 0.05 or less. Primary endpoints for this investigation will be considered to be the delta (Week 10 – Week 2) value for DEXA fat-free mass and leg press 1RM. Secondary endpoints will be delta (Week 10 – Week 2) values for DEXA fat, DEXA lean and DEXA % fat along with bench press 1RM, bench press repetitions to fatigue, leg press repetitions to fatigue, leg press volume, peak anaerobic power, mean anaerobic power, and rate of fatigue. 2 x 2 mixed factorial (group x time) ANOVA with repeated measures on time will be used to determine any statistically significant differences for time and group main effects and group x time interaction effects. Additionally, 95% confidence intervals will be constructed of the observed changes for each group to assess within and between-group changes. All data will be presented as means  $\pm$  standard deviations.

\*required

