### Familiarization and Entry (Visit 1)

At the first lab visit, participants will receive an informed consent document and will be required to give full consent before proceeding. Upon providing consent, participants will provide personal and emergency contact information before completing a healthy history and exercise history form. Study participants will receive a dietary log and will be asked to record their nutrient intake over a 3-day period (2 weekdays and 1 weekend day) for assessment of daily energy and macronutrient intake. Participants will then have initial height and body mass measurements completed. The body mass assessments taken at this time will be used as a comparison to their Visit 2 body mass to ensure participants are weight stable. To conclude this visit, participants will complete the 1RM protocol on both the bench press and leg press exercises and will complete the mid-thigh pull test, countermovement jump (CMJ) protocol and Wingate anaerobic capacity (WanT) protocol. If screened eligible due to adequate baseline strength, study participants will then be oriented to the resistance training program they will be required to follow throughout the study.

This orientation will consist of a discussion with a research team member on how to properly progress the loads they will use during each workout in addition to completing their training log in addition to discussion what dietary requirements are expected throughout the protocol. Participants will then complete a strength orientation session where an 8 to 10-repetition maximum load will be determined for all exercises they plan to utilize to begin the workout program. In addition, participants will be instructed on how to use their workout card to properly progress loads used during each workout. All participants will be required to log completion of each workout. This study visit is estimated to take 90 minutes to complete.

To document and facilitate compliance, participants will be required to log completion of each workout, send a picture of them in the gym next to exercise equipment, and schedule at least one workout per week to be completed on campus in our laboratory facilities. If individuals want to complete more workouts each week at the facilities housed at our university, they will be accommodated.

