### ***Load Progression***

In terms of load progression, participants will be asked to perform as many repetitions as they are able on their final set of each exercise. During weeks 1 – 6, if participants are able to complete 12 or more repetitions on their final set, participants will be required to increase the loads they are using to the next level. The final four weeks (weeks 7-10) of the training program, participants will be asked to complete as many repetitions as they are able on their final set. When they are able to complete 7 or more repetitions on their final set, they will be assigned to the next highest load on their progression chart for their subsequent workout. To facilitate proper load progression, four approaches will be employed by our research team. First, participants will be given a progression sheet that will guide them on what loads to use based upon their level of strength for any given exercise. During the first two study visits, this sheet will be reviewed to ensure understanding by the participants. Second, participants will be instructed to complete as many repetitions as they are able on their third and final set. This approach will allow for all participants to auto-regulate their load assignments and when they are able to complete one to two repetitions more than they are programmed to complete, they will be instructed to increase their load. Third, all study participants will be required to perform one workout per week under the direct supervision of a research team member. During this session, discussions surrounding exercise selection, load progression, etc. will be made to ensure participants understand and they are appropriately progressing the loads. Lastly, participants will be told to set a daily workout goal where their total volume-load (sets x repetitions completed x loads used) for each exercise should increase each week. Additionally, participants will be asked two compliance questions during each supervised workout: 1) are they following the load progression instructions as outlined, and 2) do they feel their unsupervised and supervised workouts are different in quality or intensity? These questions will allow for research team members to provide feedback and solutions to maximize consistency between workouts.

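### Leg press 1RM is a primary endpoint, but the training programme lets the main lower-body lift be either back squat or leg press, which adds avoidable noise to that endpoint

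*Protocol*

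**What the plan says.** Leg press 1RM appears under the primary endpoints in the Dependent Variables list. The Statistical Analysis section keeps it as one of only two primaries, defined as the Week 10 minus Week 2 "value for DEXA fat-free mass and leg press 1RM". It is therefore primary on either list. Leg press repetitions to fatigue are secondary on both lists, and the Statistical Analysis section adds leg press volume.

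The 1RM is measured "using the bench press (upper-body) and leg press (lower-body) exercises on four separate occasions (visits 2, 3, 4, and 5"). Back squat is never tested.

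Table 2 (Layout of Resistance Training Program) gives the main lower-body lift as "Back squat or leg press, 3x10" and, for the heavier block, "Back squat or leg press, 4x6". No other entry in the table offers an alternative. The corresponding upper-body entry is simply "Bench press, 3x10".

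The Visit 1 text suggests that the participant decides: "an 8 to 10-repetition maximum load will be determined for all exercises they plan to utilize to begin the workout program". During the study, the Load Progression section says only that "discussions surrounding exercise selection, load progression, etc. will be made" at the weekly supervised session. The Supplementation Protocol and the allocation paragraph match participants on fat-free mass alone. The stated analysis is a group by time ANOVA with no term for the lift trained.

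**The concern.** A 1RM result reflects strength and also familiarity with the particular lift. If some men train the tested lift twice a week and others do not train it at all, part of the spread in the leg press change will come from the choice of exercise and not from the supplement. The protocol shares this concern in principle: its Experimental Design section requires 12 months of training history in order to limit learning effects. That entry rule does not govern which lift is practised during the trial.

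What is at stake is the precision of a primary comparison with 12 men per arm. In groups this small, the numbers of squatters and leg-pressers can differ noticeably between arms by chance.

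**Working it through.** The protocol gives no power calculation, SD or expected effect for leg press 1RM, so there is no figure to reproduce. The exposure count below comes from the protocol. Everything after it rests on stated assumptions.

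**Exposure within the endpoint window (Table 2, two lower-body sessions a week, full attendance)**
- Weeks 3 to 6: 2 sessions × 3 sets × 4 weeks = 24 sets.
- Weeks 7 to 10: 2 sessions × 4 sets × 4 weeks = 32 sets.
- Total for a man training the leg press: 24 + 32 = 56 sets. For a man training the squat: 0 outside the test visits.
- The whole programme contains 68 sets, but 2 × 3 × 2 = 12 of them precede the Week 2 measurement and lie outside the primary change.

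**Assumptions**
- s is the extra gain in leg press 1RM from training that lift, in units of the SD of the change among men training the same lift. Range 0.25 to 1.0.
- p is the share choosing one of the lifts. Range 0.25 to 0.5.

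**Inflation of the SD: √(1 + p(1−p)s²)**

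| s | p = 0.25 | p = 0.5 |
|---|---|---|
| 0.25 | 1.006 | 1.008 |
| 0.5 | 1.023 | 1.031 |
| 1.0 | 1.090 | 1.118 |

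The SD therefore rises by about 1% to 12%. The required sample size rises by the square of the factor, from about 1% (1.012) to 25% (1.25).

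**Power, for scale**
- With 12 per arm and two-sided alpha 0.05 (the protocol does not state sidedness), the difference detectable with 80% power is (1.960 + 0.842) × √(2/12) = 1.14 SD, or 1.20 SD from the t distribution.
- At an assumed true difference of 1.2 SD, normal-approximation power is 83.6% with one common lift.
- With a free choice of lift, power is about 83% for s = 0.25, 81% to 82% for s = 0.5, and 75% to 77% for s = 1.0.

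**Chance imbalance**
- Suppose each man chooses either lift with probability one half. The difference D between two arms of 12 satisfies D + 12 ~ Bin(24, 0.5).
- P(|D| ≥ 4) = 1 − P(9 ≤ Bin(24, 0.5) ≤ 15) = 1 − 0.848 = 0.152.
- Over the three pairs of arms, the probability that at least one pair differs by four or more is 0.32.
- A four-man difference shifts the arm contrast by (4/12)s = s/3, which is 0.08, 0.17 or 0.33 SD for s = 0.25, 0.5 or 1.0.

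**The inflation and the imbalance are one effect**
- With p = 0.5, the difference in shares between two arms has standard deviation √(2 × 0.25/12) = 0.204.
- For s = 1.0, adding this to the basic standard error of the contrast gives √(2/12 + 0.204²) = 0.456. The basic value is √(2/12) = 0.408.
- The ratio is 0.456/0.408 = 1.118, the same factor as in the table. The two sets of figures must not be added together.

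**The case against.** **Bias.** A reader might infer that the free choice biases the comparison between supplements. The documents do not support this. Allocation is randomised and double-blind, so the choice has no systematic tendency to favour an arm. The extra spread also enters the ANOVA's own error term, so the type I error rate is preserved.

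**Contradiction over training loads.** A reader might also infer that the protocol contradicts itself, because the Visits 3 and 4 section says "New 1RM values will be used to re-assign loads during the following resistance training period" and a squatter has no squat 1RM. This does not hold either. Most lifts in Table 2 have no 1RM for anyone. Their loads come from the Visit 1 repetition-maximum session, the progression sheet and the repetition-based rule under Load Progression. A squatter's load is covered in the same way.

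**Size.** No document gives the effect of practising the tested lift. Every man also performs leg press 1RM tests at Visits 1 to 5 and leg press repetitions to failure from Visit 2 onwards, so some familiarisation precedes the Week 2 value. This stands. It is why the range used is moderate and why the effect should not be called large.

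**Existing safeguards.** Starting exercises are chosen at Visit 1, workouts are logged, and the weekly volume goal for each exercise presumes some continuity. The training card is not shown, and a statistical analysis plan that is not shown may add a covariate. So the missing model term is not a fault in itself. But these elements do not amount to a rule: no provision forbids switching lifts or requires the choice to be fixed before allocation. An analysis plan cannot standardise what was trained.

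**Tested tasks need not be trained.** The isometric mid-thigh pull is listed as primary and does not appear in Table 2. True, but that applies equally to all participants. The difficulty with the leg press is that exposure differs between men.

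**Conclusion.** The point holds as a matter of precision in a primary endpoint. The protocol requires all men to train one of its two 1RM-tested lifts and leaves the other optional, giving 56 sets against none in the window that defines the endpoint. The text establishes this with certainty.

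The consequence depends on the assumed practice effect. At 0.25 SD it is negligible, with about 1% on the SD. At 1.0 SD with an even split it adds 12% to the SD and costs about 9 percentage points of power at a true difference of 1.2 SD. The trial remains interpretable, but its leg press result would be less precise than it need be. The change is worth making because it is cheap and removes the problem at source.

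**What to change.** Preferred: in Table 2, make the tested lift common to all participants, as bench press already is. The cost is one line in the table and on the training card, and slightly less exercise choice for participants.

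If the option is kept:
- Have each man declare his lift before allocation. Table 1 marks randomisation at Visit 1, so the declaration must precede that step.
- Require him to keep that lift for all 10 weeks, and record it on the workout card.
- Include the declared lift as a factor in the analyses of leg press 1RM, repetitions to fatigue and volume, and use it in matching if feasible.

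The declaration has to come before allocation so that the factor is a baseline variable. A lift chosen or switched later is a post-randomisation variable and a less safe basis for adjustment. The cost is one recorded variable and one model term.
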